## Discussion

The study is testing a potentially efficient model of care to reduce chronic disease by utilising the current workforce and embedding brief physical activity counselling into routine care. There is strong evidence to support this intervention and the World Health Organization’s Global Action Plan on Physical Activity 2018–2030 supports this strategy as one of its’ 20 policy actions to achieve a 15% relative reduction in the global prevalence of physical inactivity by 2030 [10]. The conduct of a district-wide implementation project also has potential additional benefits above the impact on physical inactivity. It is also promoting the local health district as a “learning health system” [30] to ensure high-value care and embedding research as part of clinical practice. A potential risk is additional demands on clinicians’ time; however, the multi-faceted implementation strategy has been designed with key local stakeholder input to ensure the strategies fit within current systems.

A further potential risk is contamination between physiotherapists in intervention and control clusters. This risk has been considered carefully when designing the study. A cluster trial as opposed to an individually randomised controlled trial has been selected to reduce this risk and the trial start date has been timed with the beginning of staff rotations. It is still likely that some staff will change and rotate out of clinical teams due to unforeseen circumstances. In this instance, the physiotherapist will still be welcome to participate in the implementation strategies; however, they will not recruit any patients into the trial in their new clinical team and will be asked not to share any training resources within their new team. An existing or new member of that team not currently involved in the trial may be invited to join the study within that cluster. A final risk is the impact of COVID-19 on clinical team makeup, how routine care is delivered and opportunities for community-based physical activity for patients. The impact of COVID-19 will be carefully documented, and we will work closely with our clinical investigators to navigate this risk.

The benefits of physical activity have been well established for many years, yet the predominant research studies published are still observational studies with only 16.7% categorised as implementation and scale-up studies [62]. By using the hybrid type II design, our study will provide essential information about how this intervention can be adopted and delivered in a real-world setting while simultaneously evaluating the effectiveness of the intervention in these real-world conditions. This will provide direct evidence to policy makers as to if and how the intervention can be implemented and scaled up at a systems level to meet population health goals [62].

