Physiotherapists are ideally placed to deliver physical activity counselling within their routine healthcare interactions. Physiotherapists can effectively deliver physical activity counselling [22], and patients see them as trustworthy physical activity messengers [23]. Physiotherapists have expertise in exercise prescription for a range of different health conditions and typically see patients on multiple occasions over an extended period which is ideal for supporting behaviour change [24]. Physiotherapists surveyed around the world agree that the promotion of physical activity should be part of their clinical role [25–28]. However, current efforts to put this into practice have been sub-optimal with only 36 to 54% of physiotherapists surveyed in different countries reporting they promote physical activity beyond therapeutic exercise to 10 or more patients per month [25, 26, 28]. Physiotherapists report similar barriers to implementation as other healthcare professionals [25–28].

The Brief Physical Activity Counselling by Physiotherapists (BEHAVIOUR) cluster randomised controlled trial will aim to address this evidence-practice gap by delivering a multi-faceted implementation strategy to teams of hospital-based physiotherapists to support them to implement brief physical activity counselling into routine care, which will, in turn, increase physical activity levels of patients receiving physiotherapy. A cluster design has been chosen to avoid the risk of contamination among individual physiotherapists working together within clinical teams. Although there is strong evidence for brief physical activity counselling in healthcare, few studies have been conducted with physiotherapists working in a public hospital setting, and few studies have been conducted in lower socioeconomic areas with patients from culturally and linguistically diverse backgrounds. Consequently, we cannot be certain that the implementation of brief physical activity counselling in this setting will increase the physical activity levels of the population of interest. Therefore, we will conduct an effectiveness-implementation hybrid type II study [29] with equal interest in implementation and effectiveness outcomes. This design is particularly suited to situations such as ours where there is good buy-in in the clinical setting, but intervention effectiveness is not yet known for this particular setting and population [30].

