#### Therapist inclusion criteria

A hospital clinical team that provides a service for inpatients or outpatients within SWSLHD and has one or more physiotherapists within the team will form each of the 30 clusters. The size of clinical teams is likely to be different across different areas of physiotherapy and hospitals. Examples of clinical teams likely to be recruited include musculoskeletal outpatients, inpatient rehabilitation and pulmonary rehabilitation. For the clinical team to be included in the trial there needs to be at least one physiotherapist within the team interested in participating and who meets the following eligibility criteria: they anticipate they will remain employed within SWSLHD for the next 12 months, are either permanent or on ≥ 6-month rotation in the identified clinical team, would treat ≥ 10 new eligible adult patients within their clinical team over a 3-month period and are not working in a split role across two clinical teams that have both been identified as potential clusters for the trial to avoid potential contamination.

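### The staff-rotation rule lets an immediate-arm physiotherapist continue the implementation strategy after moving to another team, with no exception for a waitlist team, and its two safeguards only partly close that contamination route

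*Protocol article*

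**What the plan says.** The Background gives the reason for randomising teams: "A cluster design has been chosen to avoid the risk of contamination among individual physiotherapists working together within clinical teams". The therapist inclusion criteria carry the same concern into entry, requiring that a physiotherapist is "not working in a split role across two clinical teams that have both been identified as potential clusters for the trial to avoid potential contamination".

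The Discussion returns to the subject: "A further potential risk is contamination between physiotherapists in intervention and control clusters". It expects staff to move: "It is still likely that some staff will change and rotate out of clinical teams due to unforeseen circumstances". The rule for that case is that "the physiotherapist will still be welcome to participate in the implementation strategies; however, they will not recruit any patients into the trial" in their new team, and that they "will be asked not to share any training resources within their new team". The type of new team (immediate, waitlist or outside the trial) is not distinguished.

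Table 2 sets the content and timing of the strategy. Workshop 1 comes 2–3 weeks after the hospital rotation, and workshop 2 comes 3 months later. Monthly facilitation with audit and feedback runs between the two workshops, partly face to face in the clinical workplace. The Microsoft Teams collaborative lasts for the whole project.

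**The concern.** The design assumes that colleagues in one team influence each other's practice, and it keeps people who work across two clusters out at entry. The rotation rule allows a similar exposure after randomisation. A trained physiotherapist may work inside a waitlist team while still receiving support, and the paragraph that permits this is the one about contamination between arms.

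The two safeguards are limited:

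- Not recruiting keeps the mover's own new patients out of the patient-level effectiveness sample. It does not stop the mover from sharing the care of patients whom waitlist colleagues have enrolled.
- The request about sharing covers training resources only. It does not cover demonstrating or discussing counselling.
- Facilitation in the clinical workplace includes working with the team on resources and changing assessment forms. That is hard to continue from inside a waitlist team without exposing colleagues.

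The exposure at issue runs from the immediate arm into the control arm. It would raise control-arm reach and possibly control-arm activity, and so shrink both co-primary differences.

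**Working it through.** **Timing of the exposure (Table 2, therapist inclusion criteria, Abstract)**

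- Workshop 2 falls 2–3 weeks plus 3 months after the rotation starts, so workshops and facilitation end before about month 4.
- Participating staff are permanent or on rotations of at least 6 months, and the trial start is timed to the beginning of rotations. A scheduled changeover therefore comes after the workshops and facilitation have finished.
- The waitlist delay is 9 months. A changeover at month 6 falls inside the control period, but by then the main strategy element still running is the Microsoft Teams collaborative.
- Workshop 2 or facilitation would be taken while in a new team only after an unplanned move in roughly the first 4 months.

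**Reproducing the plan's power (Sample size section)**

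Inputs: 15 clusters of 10 per arm (150 patients), intracluster correlation 0.05, SD 4.4 h/week, difference 1.5 h/week, alpha 0.025. I assume a two-sided test and read the baseline term of 0.6 as a correlation.

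- Design effect = 1 + (10 − 1) × 0.05 = 1.45. Effective n = 150 / 1.45 = 103.4 per arm.
- Residual SD = 4.4 × √(1 − 0.6²) = 3.52.
- SE of the difference = 3.52 × √(2 / 103.4) = 0.489 h/week.
- Power = Φ(1.5 / 0.489 − 2.241) = 79.5%, against the stated 80%.

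Reading 0.6 as a squared correlation would give 94.9%, and no baseline adjustment would give 58.3%. Only the correlation reading reproduces the plan. On that reading, planned activity has no spare power.

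For reach (35% vs 60%), with the same design effect and 150 patients per arm assumed, a normal-approximation test with pooled null variance gives 92.0%.

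**Illustration of dilution**

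Let c be the share of control patients who receive the full immediate-arm effect. The activity difference becomes 1.5 × (1 − c), and control reach becomes 35% + 25 × c points. The documents give no value for c, so those below are assumptions.

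| c | Control patients (of 150) | Activity difference (h/week) | Power, activity | Control reach | Power, reach |
|---|---|---|---|---|---|
| 0 | 0 | 1.50 | 79.5% | 35.0% | 92.0% |
| 5% | 7.5 | 1.425 | 74.9% | 36.25% | 88.7% |
| 10% | 15 | 1.35 | 69.7% | 37.5% | 84.7% |

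For scale, c = 10% equals every patient in 1.5 average-sized waitlist teams.

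**The case against.** A reader might infer that the plan itself carries the intervention into the control arm. The documents do not support that. The new team is not said to be a waitlist team and may be in the immediate arm or outside the trial. Trial patients are those of participating physiotherapists, and the mover recruits none in the new team. What remains is indirect spill-over, a risk that the protocol names and partly mitigates. The protocol does not say whether the mover's new patients could enter the reach denominator of the new cluster.

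A reader might also infer that contamination would go unseen. It would not. Table 3 collects reach, dose delivered and fidelity in both arms, including an audit of the medical records of all patient-participants. Patients are also asked about activity advice from their physiotherapist or other providers. Raised counselling in the control arm would show. The article describes nothing that would tie it to a particular staff move.

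A third inference is a large loss of power. If three of the 15 waitlist teams were fully converted (20% of control patients), power for planned activity would be 58.3%. No text supports that input: one newcomer who recruits nobody would have to bring a whole team's practice to the trained level.

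Two further points stand. The entry criterion concerns concurrent split roles, so the rotation rule does not contradict it literally, although it sits badly with its purpose. And a mover who has attended workshop 1 keeps those skills whatever the rule says, so only part of any dilution comes from the permission to continue.

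None of this answers the central point. The rule is stated, it lacks the exception that its own paragraph calls for, and its safeguards leave several ordinary routes open.

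**Conclusion.** The concern holds as a residual contamination route left open by a stated rule. Its direction is clear: towards no difference on both co-primary outcomes. Its size is unknown, and probably small given the strategy's schedule. The main exposures are early unplanned moves into a waitlist team and continued Microsoft Teams access during the control period.

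The power figures for 5% and 10% dilution illustrate sensitivity and do not forecast what will happen. They rest on the sample-size inputs, a two-sided alpha of 0.025, the correlation reading of the baseline term, the same clustering for reach, and an assumed full immediate-arm effect in the affected patients. They show that planned activity has no margin for avoidable dilution, while reach stays above 80% in both cases. The gap does not invalidate the trial, but it is worth closing because closing it costs so little.

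**What to change.** Amend the rotation rule in the Discussion, and wherever it appears in the full protocol. If the new team is a waitlist cluster, further participation (workshop 2, facilitation and Microsoft Teams access) is deferred until that cluster receives the strategy. The rule can stay as it is for moves to immediate-arm or non-trial teams.

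Log the date and direction of every cross-arm move. Report these moves beside the control-arm reach, dose and fidelity data already being collected, so that any rise in control-arm counselling can be set against them.

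Keep the intention-to-treat analysis primary. An analysis that leaves out waitlist patients recruited after such a move would select on a post-randomisation event in one arm, so it could only be supportive.

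The cost is one sentence of protocol text and a short log. A few rotated physiotherapists complete the strategy later. The change cannot remove what was learned at workshop 1, so it narrows the route without closing it.

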## Data Availability

De-identified patient-level data for primary and secondary outcomes will be made available when the main study results are published and will be available through the University of Sydney’s open access institutional repository (htts://ses.library.usyd.edu.au/).

## Abbreviations

BEHAVIOUR: Brief Physical Activity by Physiotherapists
COM-B: Capability, Opportunity, Motivation- Behaviour theory of behaviour change
5As: Assess, Advise, Agree, Assist, Arrange
CALD: Culturally And Linguistically Diverse
SWSLHD: South Western Sydney Local Health District
CFIR: Consolidated Framework for Implementation Research
IPEQ: Incidental and Planned Exercise Questionnaire
PROMIS-29: Patient-Reported Outcomes Measurement Information System
EQ5D-5L: EuroQOL-5D
BPAQ-MI: Barriers to Physical Activity Questionnaire for People with Mobility Impairments
ICER: Incremental Cost-Effectiveness Ratios
QALY: Quality Adjusted Life Year
